### Positional Therapy Intervention

The participants in the PT intervention group will use a noninvasive vibratory device (Night Shift Device: Advanced Brain Monitoring, Inc) that is worn around the neck and promotes sleep in the nonsupine position (Figure 1 [source: [name], Liverpool Hospital, November 10, 2022])*.* The device provides a vibratory alert to the wearer when the supine position is detected and is secured at the anterior neck with a magnetic closure (Figure 2 [source: [name], Liverpool Hospital November 10, 2022]).

**Figure 1 figure1:**
[figure not shown]
Nightshift positional therapy device posterior view.

**Figure 2 figure2:**
[figure not shown]
Nightshift positional therapy anterior view.

The participants randomized to PT will be provided education by an experienced sleep therapist before commencing therapy. The device will be fitted by measuring the neck circumference and adjusted to ensure that the device does not slide down the neck. The device will be set with a 15-minute feedback delay, with vibration feedback mode on and the device location at the posterior neck. Downloads of therapy data will be obtained by an experienced sleep therapist at each study visit, where possible, as per the protocol schedule, and at the return of the device, compliance and efficacy data will be interrogated. Recording time, position, patient alert frequency, and snore data will be recorded. Feedback will be provided to study participants at each visit. Additional phone or video support will be available for participants with therapy as requested.

### Control Group

Control group participants with significant SDB at polysomnography at the 28- to 32-week gestation period and symptoms of severe EDS (ESS>15) will be identified, withdrawn from the study, and managed according to standard clinical practice under the direction of a sleep physician.

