### Eligibility Criteria

Eligible participants are defined as women aged 18 years of age and older; in early pregnancy (up to 14-week gestation period); at increased risk of metabolic complications defined as one or more of (1) BMI greater than or equal to 35 kg/m^2^, (2) previous GDM, (3) previous personal history of preeclampsia (or in mother or sister), (4) underlying renal disease, (5) maternal type 2 diabetes (pregestational), and (6) symptoms of SDB including snoring, witnessed apnea, mild excessive daytime sleepiness (EDS; which does not meet the criteria for severe EDS defined by Epworth Sleepiness Scale (ESS>15), or a fall asleep accident, or near-miss accident in the previous 12 months), or tiredness; and obstructive sleep apnea diagnosed by polysomnography defined as RDI or AHI ≥ 5.

The participants will be excluded if they have (1) a previous diagnosis of OSA on active treatment, (2) confirmed GDM or preeclampsia, (3) maternal type 1 diabetes, (4) multifetal gestation, (5) known fetal chromosomal abnormality, (6) inability to provide informed consent, and (7) severe EDS based on clinical assessment (eg, including a fall asleep motor vehicle accident or near miss, transient sleepiness while driving or at lights or needing to pull over due to sleepiness while driving, or transient sleepiness in any other dangerous situation, ie, cooking, carrying a baby) or ESS of greater than 15.

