### Interventions

All groups will have antenatal care as usual without restriction during the trial. The participants will be randomized to CPAP, PT, or control, and the participants randomized to intervention (CPAP or PT) will undertake therapy device education at the randomization visit and commence therapy on the day of randomization or as soon as is practicable. The participants will also be encouraged to use their therapy device for all sleep periods (including naps) from randomization until delivery. CPAP and PT devices will be returned following delivery or withdrawal or discontinuation from the study. The CPAP masks used by the study participants may be retained at the end of the study.

All participants will undertake polysomnography at the 28- to 32-week gestation period. CPAP or PT intervention participants will complete polysomnography at a 28- to 32-week gestation period with the device in situ to confirm treatment efficacy. CPAP will be titrated, if required, as described above. In addition, participants will be invited to complete Somte and Apnealink at 28- to 32-week gestation period, as part of the device validation substudies.

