### Participant Timeline

The participants will be reviewed monthly until the 32-week gestation period and then fortnightly until delivery, coinciding with scheduled antenatal visits where possible. The trial flow chart is depicted in Multimedia Appendix 4. The flowchart describes the participant's progression through the trial protocol and depicts the timing of the interventions.

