### Data Collection, Management, and Analysis

The complete schedule of study visits, procedures and data collection points is presented in Multimedia Appendix 5, which depicts the trial participant study visits and intervention schedule.

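### The withdrawal rule for untreated controls defines severe daytime sleepiness by ESS>15 alone, leaving out the accident, near-miss and dangerous-sleepiness alternatives that the same term carries at entry

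*Protocol article*

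**What the plan says.** The article describes severe EDS in three places.

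- **Eligibility Criteria, inclusion text.** Mild sleepiness counts as a qualifying symptom provided it falls short of "severe EDS defined by Epworth Sleepiness Scale (ESS>15), or a fall asleep accident, or near-miss accident in the previous 12 months".
- **Eligibility Criteria, exclusion text.** A woman is excluded for "severe EDS based on clinical assessment (eg, including a fall asleep motor vehicle accident or near miss, transient sleepiness while driving". The list continues to "transient sleepiness in any other dangerous situation, ie, cooking, carrying a baby) or ESS of greater than 15".
- **Control Group.** Controls with significant SDB at the 28- to 32-week polysomnography "and symptoms of severe EDS (ESS>15) will be identified, withdrawn from the study" and then managed in line with standard practice under a sleep physician.

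Three other statements bear on the point. Every randomised woman already has "obstructive sleep apnea diagnosed by polysomnography defined as RDI or AHI" of at least 5 (Eligibility Criteria). "All groups will have antenatal care as usual without restriction during the trial" (Interventions). "The participants will be reviewed monthly until the 32-week gestation period and then fortnightly until delivery" (Participant Timeline).

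**The concern.** One term has two contents, and the narrower one governs the women assigned no sleep therapy. At entry the alternatives are joined by *or*, so dangerous sleepiness is sufficient whatever the ESS. In the control rule the only content given is ESS>15. It is also joined by *and* to a sleep-study finding, and there is no reference back to the eligibility definition.

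The stake is participant safety. Staff who apply the Control Group section as written would not act through it on a drowsy-driving near miss when the ESS is 15 or less. The trial is also meant to supply the protocol for a larger one, so an uncorrected rule could be carried over to more untreated women.

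**Working it through.** No figure in the plan needs to be reproduced. The check compares the rules as written.

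**Notation**

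- E: ESS above 15.
- C: the clinical criterion in the exclusion text (fall-asleep accident, near miss, or sleepiness while driving or in another dangerous situation).
- S: significant SDB at the 28- to 32-week polysomnography.

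**Rules**

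- Exclusion at entry for severe EDS: C or E.
- Withdrawal and referral of a control: S and E.

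| Presentation | Would be excluded at entry (C or E) | Meets the control rule (S and E) |
|---|---|---|
| C yes, E yes, S yes | yes | yes |
| C no, E yes, S yes | yes | yes |
| **C yes, E no, S yes** | **yes** | **no** |
| C yes, E no, S no | yes | no |
| E yes, S no (C either way) | yes | no |

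The third row is the point. This control has significant SDB on the later study and a drowsy-driving near miss, but her ESS is 15 or less. Only the missing criterion C keeps her outside the rule. A near miss appears in both eligibility wordings (within the previous 12 months in the inclusion text), so the result does not depend on which of the two is taken as the definition.

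The last two rows fail because of the *and* with S. That requirement narrows the rule further, but it is not needed to establish that SDB is present, since OSA was shown by polysomnography before randomisation.

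**Which eligibility wording to carry over.** The inclusion text covers an accident or near miss within 12 months. The exclusion text adds transient sleepiness in dangerous situations and sets no time limit. The exclusion text is the wider of the two and is the one that keeps women out of the trial, so it is the natural match for a rule about women left untreated.

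**Reach.** The plan randomises 48 women 1:1:1, so 48 / 3 = 16 controls. The article gives no rate of severe EDS among controls, so no expected number of affected women can be calculated.

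**The case against.** The strongest reply is that the parenthesis is shorthand. The control rule reuses a term that the eligibility text has already spelled out twice, and ESS>15 may simply be its numeric marker. The article also condenses a full protocol that is not shown, and "The complete schedule of study visits, procedures and data collection points is presented in Multimedia Appendix 5", which is not shown either. That reading is possible. However, the eligibility text writes out the alternatives both times, and the control rule gives a single criterion without a cross-reference. Staff should not have to infer half of a safety rule, and if shorthand was meant, spelling it out costs nothing.

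The second reply is that other safeguards exist: unrestricted antenatal care, regular study visits, the safety committee's review of potential adverse outcomes (Safety Considerations), and immediate reporting of significant safety issues to the ethics committee (Risk Assessment and Termination of Study). These stand as mitigation. None states a sleepiness criterion, so they reduce the gap without closing it.

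A reader might also infer more than the article supports:

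- *That dangerously sleepy controls go unnoticed until the 28- to 32-week polysomnography.* The full visit schedule is not shown and may include earlier checks.
- *That ESS is collected only at baseline.* The Questionnaires section places it in baseline screening, but the Control Group section itself applies an ESS threshold to controls in connection with the later sleep study.
- *That the rule forbids action on other grounds.* It says when a control is withdrawn and does not say that other dangerous sleepiness is to be ignored.

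**Conclusion.** The inconsistency is real and can be verified from the article alone: the control rule is narrower than the plan's own entry definition of the same term. Its severity is minor. The rule covers 16 planned controls, a shorthand reading is available, and general safeguards exist. No effect on the gestational diabetes comparison, power or error rates is claimed.

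The Overview under Ethics Approval and Consent to Participate states that the last participant was recruited in December 2022 and was expected to finish in June 2024. The practical benefit therefore falls mainly on the larger trial.

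The conclusion rests on reading the parenthesis in the Control Group section literally. If the full protocol already carries the wider definition there, only the article's wording needs correcting.

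**What to change.** 1. **Definition.** In the Control Group rule, replace the ESS-only parenthesis with the exclusion wording: clinical assessment of a fall-asleep accident or near miss, or of sleepiness while driving or in another dangerous situation, since randomisation; or ESS above 15.
2. **Action.** Refer any control who meets it for sleep-physician review when it is noted at an existing visit. The later polysomnography is not needed first, because OSA is already proven at entry.
3. **Analysis.** Keep her data in the control arm for the intention-to-treat analysis. This agrees with the plan: data from women who withdraw are retained unless they ask otherwise (Overview), long-term outcomes are collected after discontinuation where agreed (Data Management), and intention-to-treat applies to primary and secondary outcomes (Statistical Methods).
4. **Where it applies.** Carry the corrected rule into the larger trial. For this trial, report any controls known to have met either the clinical or the ESS criterion.

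**Cost.** One wording change, a question or two at visits that already take place in the larger trial, and one reporting line for this one. The downside is that a few more controls would be referred and some may start treatment, which would slightly dilute the contrast with the treated arms.

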**Methods:**

This study is a randomized, controlled, open-label feasibility study in which pregnant women with an apnea-hypopnea index (AHI) or respiratory disturbance index (RDI) ≥5 are treated with CPAP (auto-titrating and fixed pressure) or positional therapy from early gestation (by 16 weeks) until delivery. The primary outcome is the feasibility of the study protocol and the development of gestational diabetes mellitus by the 28-week gestation period. Secondary outcomes include the development of hypertensive disorders of pregnancy (HDP), maternal weight gain, uterine artery blood flow, glycemic control during pregnancy (in participants who develop gestational diabetes), changes in maternal circulating biomarkers, and neonatal birthweight complications. Polysomnography at 28- to 32-week gestation period, postpartum polysomnography, therapy compliance, and patient acceptability are also assessed.

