#### Fetal Monitoring

Fetal ultrasound will be undertaken at the study site fetomaternal units (FMUs). Uterine artery blood flow (pulsatility index measurements) will be recorded at the randomization visit (12-16-week gestation period), 2-6 weeks later (average 4 weeks to 16-20-week gestation period), and at 36-week gestation period. Morphology scan (16 weeks) (may be combined with uterine artery blood flow) and growth scan (36 weeks) will be performed. Fetomaternal scans performed at study sites will be performed using ViewPoint 6 (General Electric Healthcare) by experienced sonographers supervised by physician consultants within the FMU.

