### Outcome Assessment

An oral glucose tolerance test will be undertaken for the assessment of gestational diabetes at 28 weeks (in addition to earlier testing if clinically requested). Collection of fasting blood will be followed by administration of 75 g oral glucose load, with 1 and 2 hours of blood collection. Interpretation will follow the Australasian Diabetes in Pregnancy Society (ADIPS) 2020 guidelines [38].

Blood pressure (BP) will be recorded at each study visit. Diagnosis of HDP will be defined as per the Society of Obstetric Medicine of Australia and New Zealand (SOMANZ) guidelines [39].

Anthropometric measurements (height, weight, and BMI) will be recorded during the randomization visit, and weight will be checked at subsequent study visits by study staff using hospital clinic scales.

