### Postpartum Follow-Up

RCT participants will be followed up in the clinic at 6-12 months post partum. At this time point, women will be offered repeat polysomnography, an oral glucose tolerance test (if they developed diabetes and have not already undertaken this in the postpartum period), biomarker blood, and urine collection.

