### Statistical Methods

This trial is a feasibility trial, and as such, no power calculations for the RCT were derived. We prespecified to assess the diagnostic accuracy of the home sleep tests as well as the screening questionnaires following the STARD (Standards for Reporting of Diagnostic Accuracy) guidelines. The accuracy will be assessed at various cutoff points using a receiver operating characteristic curve. The area under the receiver operating characteristic curve and positive and negative predictive values in the patient population will be derived. The first recruitment target will be 50 participants, which provides at least 80% power (α=.05) to detect a C-statistic of 0.7 when the allocation ratio is 1 (ie, 50% prevalence) and 0.75 when the allocation ratio is 2 (ie, 20% prevalence). We will be comparing Apnealink Air and SOMTE unattended PSG to attended PSG. Further exploratory analysis will be undertaken to assess whether any factors at booking, including the results of the sleep questionnaire, biomarkers, clinical factors, and history in combination with findings of unattended PSG, Apnealink, or attended PSG, are predictive of poor outcomes (either maternal or fetal, as discussed above). A composite of the combined adverse maternal outcomes and combined adverse fetal outcomes will also be assessed as an outcome. Data will be displayed as mean (SD), 95% CIs, and median (IQR) as appropriate based on data distribution. An intention-to-treat analysis will be undertaken for the primary outcome as well as the secondary outcomes. A per-protocol analysis (for primary and secondary outcomes) will also be undertaken, and both data will be presented. A *P* value of <.05 will be considered statistically significant. Where multiple analyses are undertaken, adjustments will be made for multiple comparisons. Longitudinal analysis of repeated measures will be undertaken where measurements are undertaken several times. Where differences at baseline exist between the groups, adjustments will be made statistically. Where less than 10% of any data point is missing, data will be imputed. We have preplanned an exploratory analysis of flow characteristics of all sleep tests to investigate sub-criterion flow changes related to long-term fetomaternal outcomes.

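### Control women with severe sleepiness at 28-32 weeks are removed from the study, in that arm only, which undercuts intention-to-treat for outcomes measured at later study visits

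*Protocol article*

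**What the plan says.** All places are in the protocol article.

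- **Control Group.** Controls who have significant sleep-disordered breathing at the 28-32 week sleep study together with an Epworth score above 15 "will be identified, withdrawn from the study, and managed according to standard clinical practice", under a sleep physician.
- **Interventions and CPAP Intervention.** At the same sleep study the CPAP and positional therapy arms are tested on their devices. CPAP pressure is raised if needed and the woman stays in the trial. No withdrawal rule of this kind is stated for either arm.
- **Statistical Methods.** "An intention-to-treat analysis will be undertaken for the primary outcome as well as the secondary outcomes". A per-protocol analysis is also planned. On missing data: "Where less than 10% of any data point is missing, data will be imputed".
- **Abstract, Methods.** "Secondary outcomes include the development of hypertensive disorders of pregnancy (HDP), maternal weight gain, uterine artery blood flow", among others.
- **Outcome Assessment.** "An oral glucose tolerance test will be undertaken for the assessment of gestational diabetes at 28 weeks". Blood pressure is taken at each study visit, and "weight will be checked at subsequent study visits by study staff using hospital clinic scales".
- **Fetal Monitoring.** The last uterine artery measurement is at 36 weeks, and a "growth scan (36 weeks) will be performed".
- **Postpartum Follow-Up.** "RCT participants will be followed up in the clinic at 6-12 months post partum".

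**The concern.** The rule joins two separate things: a justified change of care, and the end of trial participation. A control woman has no trial device to stop, so withdrawal from the study naturally reads as leaving the trial.

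The removal is mandatory and depends on a post-randomisation measure of the disease under study. If anyone meets the trigger, the loss occurs in the control arm alone and takes its most symptomatic women. Intention-to-treat needs outcomes on everyone as randomised, and this rule stops the collection of some of them. The imputation rule could then replace a value that might simply have been measured.

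The bias probably understates control risk, which would work against showing a treatment benefit, but the article does not establish the direction. The Introduction says the efficacy data may be used to design and power a larger trial. Carried into that trial, the rule would matter more.

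**Working it through.** **Plan's own figure.** Trial Design gives 48 women, 16 per arm: 3 × 16 = 48, which agrees. The article gives no power calculation for the randomised comparison, so there is none to reproduce.

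**Which outcomes fall after the trigger (28-32 weeks)?**

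| Outcome | Timing or source | Exposed? |
|---|---|---|
| Gestational diabetes | 28 weeks | Largely not |
| Hypertensive disorders, birth outcomes | To delivery | Probably recoverable with written agreement |
| Blood pressure | Each study visit | Partly; may be in antenatal records |
| Maternal weight | Study staff at study visits | Yes, late values |
| Uterine artery flow, growth scan | 36 weeks | Yes |
| Postpartum visit | 6-12 months | Yes |

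Visits are fortnightly after 32 weeks. A woman withdrawn at 32 weeks and delivering at 38 weeks (assumed) misses weeks 34, 36 and 38. Delivering at 40 weeks, she also misses week 40. That is 3 to 4 visits, besides the 36-week scans and the postpartum visit.

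**How many women?** The article gives no rate. Because a score above 15 is excluded at entry (Eligibility Criteria), the number may be 0 or 1. With assumed qualifying rate *p*, P(at least one of 16) = 1 − (1 − *p*)^16, and the expected number is 16*p*:

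| *p* (assumed) | P(at least one) | Expected number |
|---|---|---|
| 1% | 14.9% | 0.16 |
| 2% | 27.6% | 0.32 |
| 5% | 56.0% | 0.80 |

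**Against the 10% imputation limit.**

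- One woman: 1/16 = 6.25% of the arm and 1/48 = 2.1% of the trial, below the limit on either base.
- Two women: 2/16 = 12.5% of the arm, above the limit, but 2/48 = 4.2% of the trial, below it.

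**Effect on a continuous outcome.** If *k* withdrawn women differ from retained controls by *d* SD (assumed), the control mean shifts by (*k*/16) × *d*. The standard error of a two-arm difference with 16 per arm is √(2/16) = 0.354 SD.

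| *k* | *d* | Shift (SD) | Share of one standard error |
|---|---|---|---|
| 1 | 0.5 | 0.031 | 9% |
| 1 | 1.0 | 0.0625 | 18% |
| 2 | 0.5 | 0.0625 | 18% |
| 2 | 1.0 | 0.125 | 35% |

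**The case against.** The strongest reply is that the article already limits the damage.

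- **Follow-up after discontinuation.** Data Management provides for collecting long-term maternal and fetal outcomes after a woman leaves the trial, if she agreed in writing. This protects the main clinical events. It does not say that study weights, the 36-week scans or study visits continue.
- **Retained data.** The Overview under Ethics Approval keeps data from women who choose to withdraw. A withdrawal imposed by the protocol is not a choice, and keeping data already held creates no later measurements.
- **Repeated measures.** Statistical Methods plans longitudinal analysis, so earlier weights and the first two uterine artery measurements can be used. That softens the loss, but it cannot supply values that were never taken.
- **Asymmetry.** CPAP is titrated for residual breathing events, not for an Epworth score, and only controls are untreated. A rescue rule for controls is therefore natural. This stands: the fault lies only in ending study participation.
- **Condensed article.** Procedures after withdrawal may be fuller in the complete protocol. But the point rests on an instruction the article states, not on an omission.
- **Size and timing.** The expected number is below one at the rates assumed, the trial is an unpowered feasibility study, and the 28-32 week assessments are over. This also stands, and it limits what can be changed now.

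**Conclusion.** The concern holds. As written, the rule removes women from one arm because of post-randomisation severity, which does not fit the promised intention-to-treat analysis of secondary outcomes. The conflict is confined to measures tied to the study schedule after 28-32 weeks: the 36-week scans, late study weights, possibly some blood pressures, and the postpartum visit.

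The effect on this trial is likely small. For one woman it is 9% to 18% of a standard error, and for two 18% to 35%. These figures rest on assumed numbers withdrawn and an assumed difference of 0.5 to 1.0 SD, neither of which the article gives. The stronger reason to act is that this feasibility trial exists to refine the design of a larger one.

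**What to change.** **Wording.** In the Control Group section, replace withdrawal from the study with text such as: *she is referred to a sleep physician and treated as clinically indicated; she stays in scheduled outcome follow-up unless she declines, and is analysed as a control.* The planned per-protocol analysis is the place to set her aside once treatment starts. Use this wording in any larger trial.

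**For this trial.** Recruitment closed in December 2022, so rewording cannot change follow-up here. Report the number of such withdrawals by arm, take later outcomes from hospital records where consent allows, and include these women in the intention-to-treat control group.

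**Cost.** One sentence, one count by arm, and record extraction at two hospitals for what may be no women or one. Rescue care is unchanged. Late treatment of a few controls would slightly dilute the contrast between arms. A 36-week uterine artery measurement that was not taken cannot be recovered from records.
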